### Intervention

The intervention protocol focuses on correcting workers’ posture based on RULA by creating a fuzzy system that is helpful in most workplaces, where a large number of workers are exposed to WMSDs due to poor posture at work [42]. Exercises also include stretching and strengthening exercises of the upper limb, focusing more on the neck, hand, and wrist joints. The intervention program will be developed based on the most important predictive constructs of SCT from phase 2 of the study. The recruitment process will continue until the required sample size is reached. The researcher-made questionnaire, the standardized Nordic questionnaire, and the RULA method will be completed prior to the intervention. The intervention arm includes providing an educational intervention through the LBD process during assembly work. This intervention focuses on awareness and acquiring skills to maintain a good body posture at work and perform appropriate stretching exercises based on the most important SCT constructs. The educational content will be based on the latest national and international guidelines for the prevention of WMSDs (facts). The control group will not receive the studied intervention and will be provided them with information about ways to prevent breast cancer. The HSE expert will communicate with the participants during the intervention to teach them how to maintain a proper body posture at work and remind them to adhere to the intervention, and stretching exercises will be taught to them during breaks. Participants will receive phone calls and messages on social networks from the research team in the 12 weeks after the intervention to improve participation and adherence.

### Recruitment

Before recruiting women, the project researchers will meet with Electronics Industries personnel (e.g., industry managers, and HSE experts) to discuss the project and its requirements. Industries that agree to provide participation opportunities to their workers who are included in the study. We expect to enroll participants consecutively during a 30-day recruitment period. All potentially eligible women will be discussed directly with the aims and potential benefits of the study.

In this study, women are not included if stretching exercises are prohibited by the occupational medicine doctor, so no harm or adverse effects are expected from participating in the trial. However, a general physician (4th authors) was invited to participate in the study. He has responsibility to consider all health aspects of the project and assess all probable medical complications during the study. Moreover, all participants are asked to report any possible side effects to be assessed by physician. The control group will receive the delayed intervention after completing the 6-month follow-up questionnaire.

### Sample size

Considering that the average total number of assembly-line female workers is about 500 people, sample size was estimated 217 people using Cochran’s formula and considering the type I error (0.05). However, taking into account the 15% possible dropout, it was estimated 250 people in phase 2.

In addition, according to the study by Amit [43], who similarly used an ergonomic intervention to investigate the body posture and WMSDs in workers, to ensure sufficient power and taking into account 10% dropout, the required sample size of 40 people was calculated for each group in phase 3. This sample size was considered sufficient to test the difference between groups at power (80%) and alpha (0.05).

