**Table 1 Tab1:**
[figure not shown]
Schedule of enrolment, interviews, intervention, and assessment of the Ergonomic Intervention trial, following the Standard Protocol Items Recommended for Clinical Trials (SPIRIT) guidelines

**Table 2 Tab2:** The study overview

Phases and participant	Aim	Methods
Phase 1: Development and psychometric of tool assessment	Validation and reliability of the questionnaire and preparation of the final questionnaire	By the research team and expert panel through face and content validity, exploratory factor analysis, reliability, and impact score
Phase 2: Descriptive study		
Determining the most important predictive structures	Identifying the most important predictive structures of social cognitive theory in applying recommended behaviors	Based on a cross-sectional study
Phase 3: The randomized controlled trial		
Design the educational interventional	Step1: Set the educational content	Based on phase 2
Implementation of the intervention	Step2: Transfer concepts to the intervention group	Based on step 1in phase 3
Educational program evaluation	Step3: Investigating the effect of the educational program in the intervention group	Fuzzy RULA method, researcher-made questionnaire, Nordic questionnaire

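### The phase 2 sample of 250 covers about 13% dropout, not the stated 15%, on a requirement of 217

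*Protocol article*

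**What the plan says.** The Sample size section of the protocol article derives the phase 2 number in two steps.

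- Requirement: for a workforce described as "the average total number of assembly-line female workers is about 500 people", the "sample size was estimated 217 people using Cochran’s formula" with a type I error of 0.05. The proportion and the margin of error put into the formula are not given.
- Allowance for loss: "taking into account the 15% possible dropout, it was estimated 250 people in phase 2". How the 15% was applied is not shown.

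Table 2 describes phase 2 as "Based on a cross-sectional study", so each worker answers once and dropout here means non-response. The Data analysis section rules out replacing subjects and imputing missing values, and makes no exception for phase 2. No other section gives a different phase 2 size or loss rate.

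**The concern.** A sample size that allows for 15% dropout should leave the required number once 15% have been lost. From 250 it does not. A reader who relies on the figure will believe that 15% non-response is covered when it is not, and since subjects are not to be replaced, the plan has no stated way to make up the difference.

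What is at stake is the precision of the phase 2 survey estimates, and only slightly. The reason to raise the point is that three figures in one paragraph disagree and can be reconciled in one sentence.

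**Working it through.** **Inputs from the Sample size section:** N about 500; required n = 217; alpha = 0.05; dropout d = 15%; stated size 250.

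**Inputs assumed, because the article does not give them:** two-sided z = 1.96, proportion p = 0.5, margin e = 0.05. They are used only to check the 217 and to express the effect as a margin of error. The shortfall itself does not depend on them.

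**1. Reproduce the 217.**
- n0 = z² p(1 − p)/e² = 1.96² × 0.25/0.05² = 384.16.
- With the finite-population correction, n0/(1 + n0/N) = 384.16/(1 + 384.16/500) = 217.2.
- The variant with n0 − 1 in the denominator gives 217.5.

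Both agree with 217, so the base figure is sound under these inputs and the discrepancy lies in the dropout step.

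**2. Reproduce the 250.**
- n × (1 + d) = 217 × 1.15 = 249.55, rounded up to 250. This matches the stated figure.
- n/(1 − d) = 217/0.85 = 255.3, rounded up to 256. This does not.

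That 217 was multiplied by 1.15 is therefore an inference from the match.

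**3. What 250 delivers.**
- Respondents left at 15% loss: 250 × 0.85 = 212.5.
- Expected shortfall: 217 − 212.5 = 4.5 respondents.
- Largest loss that still leaves 217: 1 − 217/250 = 0.132, or 13.2%.
- Gap in the number recruited: 256 − 250 = 6, which is 6/250 = 2.4%.

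**4. Effect on precision.** Margin = 1.96 × √[0.25/n × (N − n)/(N − 1)], with N = 500:

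| Respondents | Margin (percentage points) |
|---|---|
| 217 | 5.01 |
| 213 | 5.09 |
| 212 | 5.11 |

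**5. Sensitivity to the size of the workforce.** With the same p, e and z, the requirement from n0/(1 + n0/N) is:

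| N | Required n |
|---|---|
| 475 | 212 |
| 480 | 213 |
| 500 | 217 |
| 520 | 221 |

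An error of 4 to 5% in N moves the requirement by about as much as the shortfall in step 3.

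**The case against.** The strongest case on the other side has four parts.

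- **The 15% may be a simple addition to the base.** The article does not say that it is a share of those recruited, and 33/217 = 15.2% fits an add-on. But the article calls the 15% dropout, and dropout is a share of the people who start. On that meaning 250 falls short. What stands is that the multiplication is inferred and should not be stated as fact.
- **The gap is within the uncertainty of the inputs.** The workforce is only approximately 500, and step 5 shows that a small error there moves the target by as much. This stands as an argument about size: 256 is no more exact than its inputs. It does not make 217, 15% and 250 consistent with one another.
- **Construct selection does not hang on it.** Because the intervention is built on the predictors found in phase 2, a reader might infer that the shortfall endangers the choice of social cognitive theory constructs. The article does not support this. Cochran's formula sets the precision of a proportion, whereas the predictors are to be chosen with a Bayesian network, and nothing shows that the choice would differ between 212 and 217 respondents.
- **The trial proper is untouched.** A reader might also infer that the randomised comparison is too small as a result. It has a separate calculation (40 per group, 10% dropout, 80% power) into which the phase 2 figure does not enter.

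That the article condenses a fuller protocol does not help here, because the point concerns figures that are stated, not details left out.

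**Conclusion.** The point holds as a minor internal inconsistency. Using only the article's own 217, 15% and 250, the stated size leaves about 212 respondents at the stated loss and tolerates 13.2% instead of 15%. This rests on reading dropout as a share of those recruited, which is the ordinary meaning.

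The consequence is confined to the precision of the phase 2 survey: about 0.1 percentage point on the margin of error, given p = 0.5, a 5-point margin, z = 1.96 and N = 500, all but the last of which are assumed. No effect on construct selection has been shown, and no conclusion of the phase 3 comparison depends on 250 against 256.

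**What to change.** Amend one sentence in the Sample size section, in either of two ways.

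1. **Keep 250 and say what it delivers.** Either state that it leaves 217 respondents at up to about 13% non-response, or state that at 15% non-response it yields about 212. If the second, give the margin of about 5.1 points, provided that p = 0.5 and a 5-point margin were the inputs used. This needs no further recruitment and is enough.
2. **State 256** (217/0.85, rounded up) and keep the 15%. This costs at most six more one-off questionnaires.

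In either case, show how the allowance was applied and give the proportion and margin behind the 217, so that a reader can follow both steps.

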### Sampling

The industries will be randomly allocated to the control and intervention groups by throwing dice. Then, among the assembly-line female workers in each industrial unit, the eligible ones are determined and 40 participants randomly selected (a list of workers is prepared and based on table of random numbers) from each industry. The randomization unit is the industrial unit. Opaque sealed envelopes will be used to ensure the allocation concealment. The researcher will generate the allocation sequence, enroll participants, and assign them to interventions.

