### Blinding

The control group will also be provided with an educational intervention that is not related to the main objective of the research, and since the control and intervention groups are assigned into two separate industries, the workers will be unaware of the group assignment. Since the participants will be assigned a code, data and outcome analysis will be unaware of the names of the participants and the control and intervention groups. The main researcher of the study will not be blinded.

There are no known circumstances in which emergency unblinding would be required; however, if there are compelling reasons, such as if the information is needed for recruitment purposes, the principal investigator will provide permission for unblinding. The protocol deviation form should be registered in the trial database.

Participants’ personal information is assigned a unique identification code, stored in a password-protected format, and accessible only to the principal investigator. Participants cannot be identified in manuscripts, reports, or research-related presentations. Data that will be entered into SPSS will be double checked to promote data quality.

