### Data analysis

Data analysis will be performed using intention-to-treat analysis in the SPSS ver. 19 software and Bayesian network model. First, exploratory factor analysis will be conducted to assess construct validity after confirming sampling adequacy based on the KMO and Bartlett’s test statistic. Second, the Bayesian network model will be used to determine the variables affecting the use of preventive behaviors for MSDs.

Third, data distribution will be investigated using the Shapiro–Wilk test. Fisher’s exact test will be used for qualitative data; independent *t*-test or Mann–Whitney test will be used to determine the mean score of the studied constructs in two control and intervention groups. Pearson and Spearman correlation tests will be used for parametric data and Kendall rank correlation for non-parametric data. Moreover, to compare the difference between the values obtained before the intervention and 3, 12, and 24 weeks after the intervention in each group, generalized mixed models of repeated measure analysis of variance will be used. Bonferroni’s correction will be used for multiple primary outcomes. The difference between the means of the independent groups will also be calculated at 95% confidence interval. *P*-value < 0.05 will be considered as the statistically significant level. No replacement of study subjects or imputation of missing data will be carried out.

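### The 80% power claim and the worker-level between-arm tests ignore that whole industrial units are randomised, apparently one per arm, so no valid between-arm test exists as planned

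*Protocol article*

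**What the plan says.** **Design.** The Sampling section of the protocol article states: "The industries will be randomly allocated to the control and intervention groups by throwing dice", and again: "The randomization unit is the industrial unit". Within the allocated plants it takes "40 participants randomly selected (a list of workers is prepared and based on table of random numbers) from each industry". The Blinding section argues that workers will not know their allocation "since the control and intervention groups are assigned into two separate industries".

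**Sample size.** For phase 3: "taking into account 10% dropout, the required sample size of 40 people was calculated for each group in phase 3". The basis is one cited study "who similarly used an ergonomic intervention to investigate the body posture and WMSDs in workers". No difference, standard deviation, ICC, design effect or number of units is given. The section concludes: "This sample size was considered sufficient to test the difference between groups at power (80%) and alpha (0.05".

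**Analysis.** The Data analysis section names Fisher's exact test for qualitative data, and says that an independent t-test or Mann-Whitney "test will be used to determine the mean score of the studied constructs in two control and intervention groups". Change over the four time points within each group is assigned to a mixed or repeated-measures model. Bonferroni's correction applies to multiple primary outcomes, and the Outcomes section names two main outcomes. No term for the industrial unit appears.

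**The concern.** The t-test, Mann-Whitney and Fisher's exact test treat each worker as an independent observation. When a whole plant is allocated, everything that makes its workers alike moves with the allocation. The variance of the difference between arms then contains a between-plant part that these tests do not estimate. Their standard errors are too small, and they reject too often.

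The power statement has the same gap: a per-person number with only a dropout allowance describes a trial that randomises workers. With a single plant per arm, any existing difference between the two plants is indistinguishable from an effect of the training. A result at P<0.05 could be reported as a randomised effect when it shows only that two plants differ.

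**Working it through.** **Number of units.** 40 per group (Sample size) divided by 40 per industry (Sampling) is 1 industry per arm. This agrees with the two separate industries in the Blinding section.

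**The plan's own figure.** 40 × 0.9 = 36 evaluable per group, and 36/0.9 = 40, so the dropout step is consistent. The 36 cannot be derived, because no effect size or SD is stated. Solving backwards for independent workers (two-sided 0.05 assumed, since sidedness is not stated; 80% power):

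- normal approximation: d = (1.960 + 0.842) × √(2/36) = 0.66
- t distribution: d = 0.67

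So 80% corresponds to d of about 0.67 with ICC = 0.

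**Type I error of the planned worker-level test.** With m = 36 workers in one unit per arm, the variance of an arm mean is multiplied by DE = 1 + (36 − 1) × ICC. The true error of the nominal 5% test is 2 × [1 − Φ(1.96/√DE)]. The ICC values are assumed.

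| ICC | DE | 1.96/√DE | True type I error |
|---|---|---|---|
| 0 | 1.00 | 1.96 | 5% |
| 0.01 | 1.35 | 1.69 | 9% |
| 0.02 | 1.70 | 1.50 | 13% |
| 0.05 | 2.75 | 1.18 | 24% |
| 0.10 | 4.50 | 0.92 | 36% |

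The formula is slightly lenient, because with one unit per arm the observed within-arm variance is only (1 − ICC) of the total. A simulation of 40,000 trials per ICC value gave 9.4%, 13.8%, 25.0% and 37.4% for the four non-zero ICCs.

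**Whether a correct test is available.** A test on unit means with k units per arm has 2k − 2 degrees of freedom. For k = 1 this is 2 × 1 − 2 = 0. A random intercept for unit fails for the same reason: with one unit per arm it coincides with treatment.

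**Illustration with several units.** Spread the same 36 evaluable workers per arm over k = 5 units, so m = 36/5 = 7.2, with d = 0.67 and ICC = 0.05:

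- DE = 1 + (7.2 − 1) × 0.05 = 1.31
- standard error = √(2 × 1.31/36) = 0.270
- noncentrality = 0.67/0.270 = 2.48
- degrees of freedom = 2 × 5 − 2 = 8
- two-sided 0.05 (critical t 2.306): power about 59%
- Bonferroni 0.05/2 = 0.025 (critical t 2.752): power about 44%

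At ICC = 0 the same layout has about 70% power at 0.05, so part of the loss comes from having only 8 degrees of freedom.

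**The case against.** **The inputs are not in the document.** The ICC range is assumed and d is solved backwards from the claim. This stands as a limit on the size of the error, not on its direction: any ICC above 0 raises the type I error above nominal.

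**A separate analysis plan may add a unit term.** It may, but the article states the worker-level tests and the 80%, and a later unit term would not make either correct. With one unit per arm it could not be estimated.

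**There may be more than two industries.** The Sampling section uses an open plural. If so, a unit-level analysis becomes possible, but the stated power and tests still ignore the units.

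Three stronger readings are tempting, and the document does not support them:

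- *All planned tests are invalid.* The factor analysis, Bayesian network and correlations do not compare arms. The repeated-measures model is worded as change over time within each group, where a shared plant effect matters less. The criticism is confined to the between-arm tests, and to the planned 95% interval for the difference in means if it uses worker-level standard errors.
- *The sample size arithmetic is wrong.* It is consistent as far as it can be checked. The fault is a mismatch between design and analysis.
- *The trial has a smaller effective sample but a valid test.* Dividing 36 by the design effect gives about 13 per arm at ICC 0.05, which suggests a weaker test that could still be run. With 0 degrees of freedom there is none.

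The document also does not say that workers in a plant share workstations or supervisors. It says only that an HSE expert teaches in the workplace, so the degree of correlation remains an assumption.

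**Conclusion.** The point holds for the power claim and the worker-level between-arm tests. The 80% is correct only for ICC = 0, at d of about 0.67 and alpha 0.05. Under the assumed ICC range of 0.01 to 0.10, the nominal 5% between-arm test rejects a true null in about 9% to 36% of trials. Reading the Sample size, Sampling and Blinding sections together, there is one industry per arm. The intervention effect is then fully confounded with the plant, and neither more workers per plant nor another model can separate the two. The direction is secure for any positive ICC; the percentages depend on the assumed ICC and 36 evaluable workers per arm.

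**What to change.** The passages are wrong as written, and the change depends on the number of industries.

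**If two industries are kept:**

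- Delete the 80% power statement from the Sample size section.
- In the Data analysis section, present between-arm differences as a descriptive two-site comparison, state that the intervention effect is confounded with the plant, and do not present worker-level P-values as valid for a randomised effect.

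This is a wording change. Its price is a weaker conclusion.

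**If several industries are allocated per arm:**

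- State k, the workers per unit and the assumed ICC range.
- Recompute power with the design effect, 2k − 2 degrees of freedom and the Bonferroni level of 0.025 for the two main outcomes. In the five-unit illustration the figure to report is about 44%; neither 59% nor 80% would be right.
- Replace the worker-level between-arm tests with a mixed model that has a random intercept for industrial unit and small-sample degrees of freedom, or with a t-test on unit means.

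This is more than rewording. Even with the same 80 workers, more industries must agree to take part and the training must be delivered at more sites. The stated power will also look less favourable.

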### Sampling

The industries will be randomly allocated to the control and intervention groups by throwing dice. Then, among the assembly-line female workers in each industrial unit, the eligible ones are determined and 40 participants randomly selected (a list of workers is prepared and based on table of random numbers) from each industry. The randomization unit is the industrial unit. Opaque sealed envelopes will be used to ensure the allocation concealment. The researcher will generate the allocation sequence, enroll participants, and assign them to interventions.

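### Industries are allocated before workers are screened, drawn and consented, so the sealed envelopes cannot conceal a worker's arm from the person enrolling her

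*Protocol article*

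**What the plan says.** The protocol article's Sampling section sets out the steps in order:

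- Allocation: "The industries will be randomly allocated to the control and intervention groups by throwing dice".
- Screening and selection: "Then, among the assembly-line female workers in each industrial unit, the eligible ones are determined and 40 participants randomly selected". The method of selection is given in brackets: "a list of workers is prepared and based on table of random numbers".
- Unit: "The randomization unit is the industrial unit".
- Concealment: "Opaque sealed envelopes will be used to ensure the allocation concealment".
- Roles: "The researcher will generate the allocation sequence, enroll participants, and assign them to interventions".

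The Blinding section says that the two arms sit in two separate industries, that workers will not know their group, and that the main researcher is not blinded. It foresees no emergency unblinding, but it gives an example of a compelling reason: "such as if the information is needed for recruitment purposes, the principal investigator will provide permission for unblinding".

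The Recruitment section has project researchers meet industry managers and safety experts before any women are recruited, and it adds: "We expect to enroll participants consecutively during a 30-day recruitment period". The Study design section describes participation as voluntary.

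**The concern.** Allocation concealment means that whoever decides on a person's entry cannot know which arm she would join. In a cluster design with recruitment after allocation, this protection is lost for individuals even when the clusters were allocated fairly. Knowledge of the arm can then influence who is judged able to take part for six months, how the study is presented and who agrees to join.

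The resulting difference between arms would be present before any intervention, and randomisation would not balance it. It could be mistaken for an effect on posture score or on adherence to stretching, the two main outcomes. Analysis cannot reliably undo it, because workers who were screened out or who declined leave no outcome data.

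**Working it through.** The point concerns procedure, and the plan gives no figure to reproduce. The check is to follow one worker through the stated steps.

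1. **When is her arm fixed?** At the dice throw. The randomisation unit is the industrial unit (Sampling), and each arm is a separate industry (Blinding), so her employer determines her arm.
2. **What follows the dice throw?** The sentence on eligibility and selection comes next and opens with a word of sequence. Screening and the draw of 40 therefore follow allocation. The approach to the selected workers and their consent must come later still.
3. **Does the enroller know the arm?** Yes. The same researcher generates the sequence, enrols and assigns. This holds whether or not that person is the unblinded main researcher of the Blinding section.
4. **What can an envelope conceal at enrolment?** Nothing about the worker. There is no worker-level sequence, and her industry's arm is already known.
5. **Could it conceal anything about an industry?** Possibly. If both industries had agreed before the throw, neither their agreement nor the researcher's choice of industries could depend on the result. The Recruitment section puts the meetings before the recruitment of women, but does not place them relative to the dice.
6. **Which steps remain open to influence?**
   - Eligibility: Eligibility criteria includes the ability to take part for at least six months, which calls for judgement. Age, sex, literacy and pregnancy leave little room for it.
   - Draw: the random-number table limits hand-picking from the list. It does not protect the decision about who is on the list.
   - Approach and consent: under Recruitment, women are told the aims and potential benefits of the study, and participation is voluntary. Staff who know the arm can present it differently.
7. **Does baseline measurement come before allocation?** The Intervention section puts the questionnaires and the RULA assessment before the intervention, which still allows them to follow allocation.
8. **Does the unblinding clause help?** No. It names recruitment as a reason to reveal allocation, and recruitment is the stage at which allocation most needs to stay hidden.

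**The case against.** The best defence is that real safeguards exist. A random draw from a list restricts selection by hand. Workers are said not to know their arm, and controls receive unrelated education, so consent should not differ through the workers' own knowledge. Most entry criteria are objective, and Recruitment assigns the prohibition on stretching to the occupational medicine doctor. All of this stands and narrows the route for bias to the judgemental part of eligibility and the conduct of staff who know the arm. It does not support the envelope claim for workers.

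Several stronger readings are tempting, but the text does not carry them:

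- **That the researcher decides eligibility.** Sampling uses the passive and names no one.
- **That the enroller is stated to be unblinded.** Sampling refers to the researcher and Blinding to the main researcher. That they are the same person is an inference, and the point does not need it.
- **That concealment is absent altogether.** At industry level it depends on an order of events that is not stated.
- **That random selection and consecutive enrolment contradict each other.** Workers drawn at random can be enrolled one after another over 30 days. The wording is unclear, but no conflict is shown.
- **That a false-positive rate can be attached.** With 40 × 0.90 = 36 evaluable per arm, the probability of rejection under a pure selection shift of b SD is P(|Z + b√18| > c). For a 5% test (c = 1.99), assumed shifts of 0.2 and 0.3 SD give about 13% and 24%. The Data analysis section applies Bonferroni to the primary outcomes. With two outcomes, each tested at 2.5%, the same shifts give roughly 8% and 15%. Nothing in the document supports either shift, so these figures carry no weight in the conclusion.

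**Conclusion.** The concern holds at worker level. As written, allocation precedes eligibility, selection, approach and consent. The person who enrols also generates the sequence and assigns, so opaque envelopes cannot deliver the concealment claimed for them. The clause allowing unblinding for recruitment works in the same wrong direction.

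The conclusion rests on reading the Sampling steps in the order printed and on each arm being one industry, as Blinding says. The direction and size of any bias cannot be estimated from the document, and the random draw and the workers' stated unawareness should keep it smaller than in an open selection.

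A reader might infer that correcting the order would make the arms comparable. It would not. With one industry per arm, any difference between the two workplaces remains inseparable from the intervention. That is a separate problem. The correction here removes only selection after allocation.

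**What to change.** If allocation has not yet taken place:

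1. Obtain both industries' agreement. In both, list the workers, screen them, draw the 40 at random, take consent and complete the baseline RULA and questionnaires. Allocate only after that, and state this order in Sampling.
2. Have an existing team member with no role in eligibility or enrolment make the allocation draw. Because the team physician is responsible for the health aspects of the project, that person's independence from medical eligibility would have to be established first.
3. Delete recruitment as an example of a reason for unblinding.
4. Clarify in Recruitment that consecutive enrolment refers to the workers already drawn at random.

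The protocol is dated 24 January 2023 and expects recruitment to finish by August 2023, so allocation may already have happened. In that case, withdraw the envelope claim, state that recruitment followed allocation, and report the numbers eligible, approached and consenting in each arm.

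The cost is revised wording and a changed sequence, with no extra participants or measurements. The one drawback is that the intervention cannot begin until baseline is complete in both industries.
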